### Intervention

Once the centre is randomised to receive the intervention, all eligible women, with suspected or diagnosed pre-eclampsia, will have sFlt-1/PlGF measurement and fullPIERS assessment performed as part of their routine care, and both results will be revealed to the care providers. sFlt-1 and PlGF will be measured using the Elecsys® Preeclampsia Platform (Roche Diagnostics) and the results will be entered onto the trial-specific MedSciNet database. Risk stratification using fullPIERS will be performed directly using a pre-defined risk scoring system integrated within the MedSciNet database. These results will be available within an amount of time (3–4 h), which permits for timely clinical decision-making.

The results will stratify eligible pregnant women into low-risk or not low-risk for adverse outcomes according to combined assessments of sFlt-1/PlGF and fullPIERS (Fig. 2). Low risk will be considered when sFlt-1/PlGF ≤38 and fullPIERS < 10% risk. The output provided by the platform will be: “Reassuring - low risk for adverse outcomes”, with recommendations that delivery be delayed unless the clinical condition deteriorates. Testing should be repeated at least twice weekly with fullPIERS and at least weekly with sFlt-1/PlGF for reassessment*.* The output for women stratified as not low risk (sFlt-1/PlGF> 38 and/or fullPIERS ≥10% risk) will be: Non-reassuring, with recommendations to increase surveillance based on WHO guidelines about delivery, including the need for preventative therapy with corticosteroids for fetal benefits, antihypertensive therapy and magnesium sulphate for seizure prophylaxis [3]. It is important to emphasize that the PREPARE protocol does not recommend delivery based on sFlt-1/PlGF> 38 and/or fullPIERS ≥10% risk. In these situations the PREPARE protocol recommends increased surveillance while delivery indications are based to local protocols and WHO criteria. Active knowledge transfer is a crucial part of this study and it will be directed primarily to clinicians, obstetric nurses, and technical staff.

**Fig. 2 Fig2:**
[figure not shown]
The PREPARE protocol for the intervention proposed. The care providers of women, who are low risk by both sFlt-1/PlGF and fullPIERS, will be informed of the woman’s risk status in 3–4 h, with a recommendation that delivery be delayed unless the clinical condition deteriorates. Women will be reassessed at least twice weekly with fullPIERS and at least weekly with sFlt-1/PlGF

### Outcome measures

#### Primary

Proportion of women delivered in the centres with preterm pre-eclampsia (deliveries with preterm pre-eclampsia/ total deliveries), where preterm is < 37 weeks’ gestation.

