Two methods of risk stratification will be used to help obstetricians to make decisions regarding the best timing for delivery for women with suspected or diagnosed preterm PE. This application extends a recent Latin American trial of conservative management of very preterm PE, which did not have access to these objective risk stratifiers [12]. The first component of the PREPARE study intervention is the fullPIERS risk stratification algorithm. The fullPIERS algorithm is based on maternal symptoms, signs, and laboratory tests to accurately identify women at increased risk for maternal complications related to PE [13]. It predicts adverse maternal outcomes (AUROC 0.88) within 48 h but also performs well for up to the next seven days. Therefore, the fullPIERS model is able to identify those pregnant women who do not need immediate delivery, but do need continuing close surveillance. The second method uses the biomarker sFlt-1/PlGF ratio as a prognostic indicator for clinical need for delivery [14, 15]. In a prospective, multicentre, observational study, Zeisler et al. used a cohort of 500 women with suspected PE at less than 37 weeks to determine that sFlt-1/PlGF ratio cut-off of 38 had predictive value to indicate time to delivery. In this cohort, the negative predictive value of developing PE within one week was 98.9% with sensitivity of 88.2% and specificity of 80% [14]. In a validation cohort of additional 550 women, a cut-off of sFlt-1/PlGF ratio of 38 or lower had a negative predictive value of 99.3% for the development of PE within one week, sensitivity of 80% and specificity of 78.3%. Either fullPIERS or sFlt-1/PlGF strategies have more than 98% negative predictive value for adverse outcomes.

We will perform both of these determinations on women presenting with suspected or diagnosed PE in which hospital admission or delivery would usually be considered with conventional Brazilian practice. The fullPIERS assessment will be repeated twice weekly and sFlt-1/PlGF ratio weekly. For women with PE who are low risk by both assessments, we will recommend to care providers that delivery be delayed safely. Since greater than 95% of deliveries in Brazil occur in the hospital setting, this intervention is likely to have a high impact on reducing the number of unnecessary, iatrogenic preterm deliveries related to PE.

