**Fig. 1 Fig1:**
[figure not shown]
Description of randomisation and implementation of the intervention for the Stepped Wedge design. There will be an initial four-month period of baseline data collection at hospitals, during which none of the centres will be exposed to the intervention. Subsequently, every four months, one centre will be randomised to the intervention. Four months prior to implementation, the centre will be engaged in a programme of intensive knowledge transfer, followed by one month of transition

Routine clinical data will be collected for the trial on all pregnant women with suspected or diagnosed pre-eclampsia that present to the participating centres between 20 + 0 and 36 + 6 weeks’ gestation.

In addition, they will be invited to sign the informed consent form, and provide additional samples for research purposes.

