### Data management

All demographic and clinical data will be entered into a secure Internet based database designed and maintained by MedSciNetAB. This is the Global Pre-eclampsia Database which has been developed by CoLab (Global Pregnancy Collaboration) with MedSciNet and modified as appropriate for PREPARE. MedSciNet databases provide a secure and globally accessible data entry system that conforms to relevant FDA, NIH, and HL7 standards, guidelines, and recommendations (http://medscinet.com/projects.aspx). This data solution has been used for numerous clinical trials and studies globally, including several led by PIs of this project, and WHO studies in low to middle income countries. Data is held on software deployed on servers located in a data centre in Stockholm, operated in compliance with ISO27000 and SAS-70 standards and with 24 × 7 monitoring. Predefined reports are generated from an inventory, which logs sample deposition and removal.

Two research managers of the study will monitor data completion regularly and inform responsible researchers at each centre regarding problems to be addressed and corrected. All data must be completed up to 4 weeks after expected date to deliver.

Development of a biorrepository to test for unique pre-eclampsia features in Brazil, and for future mechanistic studies Additional file 2.

All women admitted with suspected or diagnosed pre-eclampsia will be invite to provide 20 mL of blood and 10 mL of urine. Therefore, plasma, serum, cells for DNA and urine will be stored in the facilities for long term sample storage (Biorepository). This biorrepository will be located at the Study Centre Laboratory, Medical School, Botucatu São Paulo State University, where -80 °C freezers with a nitrogen back-up system purchased for this purpose will be installed in the Laboratory for Clinical and Experimental Investigation with emergency power and alarms. In the event of freezer malfunction back-up freezers are available at this site for use during freezer repair. Informed consent will be requested for this purpose and will be taken by nurses that make part of the groups in each participant centre.

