### Statistical issues

#### Sample size

The primary aim is to test whether care targeted at preventing unnecessary delivery of women with pre-eclampsia will reduce the proportion of women delivered in the centres with preterm pre-eclampsia (deliveries with preterm pre-eclampsia/total deliveries). The power calculation depends on estimates of the total number of births, current pre-eclampsia prevalence and proportion with preterm deliveries from the seven centres (which have already agreed to participate). We estimate the mean number of infants born in each month per centre to be 330, and that of these ~ 5% will be born to women with pre-eclampsia. The preterm rate among those women with pre-eclampsia is approximately 36%. Therefore each month, there will be the potential to enter 17 women with pre-eclampsia, of whom approximately 6 would deliver prematurely, and outcome data will be available for approximately 700 deliveries of women with preterm pre-eclampsia. There is limited information on likely intracluster correlation (ICC) for this outcome in this setting and so we have explored sensitivity to a range of values.

Power calculations for stepped wedge cluster trials were as described in Hussy and Hughs [18]. Assuming that seven centres take part and allowing for a one month transition phase, and that in each centre there are approximately 17 cases of pre-eclampsia and 330 deliveries per month (with outcome data available for all deliveries), this study will have 89.6% power to detect a reduction in preterm deliveries associated with pre-eclampsia in the study centres from a population estimate of 1.5 to 1.0%, representing a 33% risk reduction, and 79.6% power to detect a reduction from 2.0 to 1.5% (25% risk reduction). Although the ICC is included in the power calculation, the design was found to be insensitive to the ICC and sensitivity analyses showed that these calculations were robust to larger magnitudes of ICCs.

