### Data analysis

Hospital baseline characteristics of pregnancy outcomes to be collected throughout the data retrieval period will include numbers of women developing pre-eclampsia, women with preterm pre-eclampsia, gestational age at delivery of all hospital deliveries, and maternal and neonatal inpatient nights in women with pre-eclampsia. These baseline characteristics will be compared between exposure and non-exposure to the intervention and will be summarised by their means and standard deviations, medians and inter-quartile ranges, or numbers and percentages as appropriate. Centres will be classified as being exposed to the intervention one month after the centre was randomised to the intervention, and outcomes during the transition months will not be included.

The primary goal of the study is to test whether a care pathway targeted at preventing unnecessary delivery of women with pre-eclampsia will reduce the proportion of women delivered in the centres with preterm pre-eclampsia (deliveries with preterm pre-eclampsia/total deliveries). In statistical terms this null-hypothesis (no difference) can be tested using a mixed effects logistic regression model, with an indicator of whether the centre was exposed to the intervention as the dependent variable. Important independent variables to consider are the clustering effect (i.e. effect of centre), calendar time effect (since the intervention is sequentially rolled-out) and an indicator of intervention exposure for each centre at each time point; in additional to adjustment for other characteristics. Both individual and cluster level covariates to be included in the adjustment will be pre-specified and will include maternal age, parity, pre-existing chronic hypertension or other risk factors for prematurity. Null hypotheses and analyses for secondary outcomes take a similar form to that for the primary outcome, with appropriate link functions in the generalized linear mixed model. Summary treatment effect estimates will be reported (odds ratios or risk ratios) along with 95% CIs. These models will be fitted using population-averaged models using mixed effects methods in Stata version 14.2 or later (StataCorp, College Station, Texas).

The final trial dataset access will be limited to the authors of this study protocol.

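### The primary outcome counts only deliveries in the participating centres, so a deferred woman who delivers preterm elsewhere lowers the rate with no preterm birth averted

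*Protocol article*

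**What the plan says.** Under Outcome measures, the primary outcome is the "Proportion of women delivered in the centres with preterm pre-eclampsia (deliveries with preterm pre-eclampsia/ total deliveries", with preterm meaning before 37 weeks. The Sample size and Data analysis sections repeat the same ratio. The power calculation takes 330 deliveries per centre per month, "with outcome data available for all deliveries". Data analysis lists "gestational age at delivery of all hospital deliveries" among the hospital-level characteristics to be collected.

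Women enter the study by presenting at a centre, not by delivering there. The Background describes them as "women presenting with suspected or diagnosed PE in which hospital admission or delivery would usually be considered with conventional Brazilian practice". Under Intervention, women with a low sFlt-1/PlGF ratio and a low fullPIERS score are reported as reassuring, "with recommendations that delivery be delayed unless the clinical condition deteriorates". Their follow-up is specified: "Testing should be repeated at least twice weekly with fullPIERS and at least weekly with sFlt-1/PlGF for reassessment".

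Data collection is wider than the primary outcome. The text after Fig. 1 says "Routine clinical data will be collected for the trial on all pregnant women with suspected or diagnosed pre-eclampsia that present to the participating centres". Data management adds "All data must be completed up to 4 weeks after expected date to deliver". Prolongation of pregnancy, a secondary outcome, needs each woman's delivery date.

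The article does not say how the primary outcome treats a woman who is seen at a centre and delivers at another hospital.

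**The concern.** Being delivered in a centre is a condition of being counted, and the intervention can affect that condition. A woman delivered at presentation is an event if she is preterm. A woman whose delivery is deferred has an interval in which she may come to deliver at a different hospital. If that delivery is preterm with pre-eclampsia, she disappears from the ratio and the centre's rate improves, although the preterm birth took place.

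A favourable primary result could then mix preterm births averted with preterm births moved, and the stated outcome alone cannot separate them. The target effect is small in absolute terms, so a few moved deliveries per centre would matter.

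**Working it through.** **Inputs from the article.** Seven centres; 32 months of data; one crossover every four months after a four-month baseline, hence 8 periods; one transition month dropped per centre; 330 deliveries per centre-month; scenarios 1.5% to 1.0% and 2.0% to 1.5%; stated power 89.6% and 79.6%.

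**Assumptions.** Two-sided alpha 0.05; ICC not stated, so 0.001 to 0.05 is used; the leaked share f is not given anywhere and is purely assumed.

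**1. The plan's own figure.** I used the Hussey-Hughes variance with fixed period effects and a random centre effect; power = Phi(difference/SE - 1.96).
- Variance at the control rate, ICC 0.001: SE 0.158 and 0.182 percentage points, power 88.4% and 78.3%.
- Variance at the mid-rate, ICC 0.01: SE 0.149 and 0.176 points, power 91.8% and 81.0%.

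These bracket the stated 89.6% and 79.6%. The power statement reproduces approximately and is not in dispute here.

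**2. Size of the target in events.** 330 x (1.5% - 1.0%) = 330 x 0.5% = 1.65 events per centre-month; the same for 2.0% to 1.5%.

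**3. Effect of moved preterm deliveries.** Let a fraction f of preterm pre-eclampsia deliveries occur preterm elsewhere, with true rate p unchanged. Both numerator and denominator lose pf, so the observed rate is p(1 - f)/(1 - pf).
- One moved delivery at the plan's 5% x 36% = 1.8%: 330 x 1.8% = 5.94 events, and (5.94 - 1)/(330 - 1) = 4.94/329 = 1.50%, an apparent relative reduction of about 17%.
- To produce the whole target effect: f = 33.7% at base 1.5%, or 25.4% at base 2.0%, each about 1.7 moved deliveries per centre-month.

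**4. Chance of a falsely favourable result.** No true effect, leakage f in the intervention phase and none in the control phase; mid-rate variance, ICC 0.01; probability = Phi(z - 1.96).

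| Base rate | f | Observed rate | SE (points) | z | Probability |
|---|---|---|---|---|---|
| 1.5% | 5% | 1.426% | 0.161 | 0.46 | 6.7% |
| 1.5% | 10% | 1.352% | 0.159 | 0.93 | 15.1% |
| 2.0% | 5% | 1.902% | 0.186 | 0.53 | 7.6% |
| 2.0% | 10% | 1.804% | 0.184 | 1.07 | 18.7% |

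At ICC 0.001 the four probabilities are 6.8%, 15.8%, 7.8% and 19.6%. Rounded across these settings, they are 7-8% for f = 5% and 15-20% for f = 10%.

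**5. Two cases with little or no bias.**
- Term delivery elsewhere. With p = 1.5% and 20% of would-be preterm cases delivering at term elsewhere, the true rate is 1.200% and the observed rate 0.012/(1 - 0.003) = 1.204%.
- Equal leakage. At f = 5% in both phases the observed rate is 1.426% in each, and the difference is zero. Only the excess in the intervention phase biases the comparison.

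**The case against.** The strongest reply is that departure from the centre is conjecture. Nothing says that deferred women are discharged or transferred, and they are to be retested at least twice weekly. Closer surveillance could even keep more women in the centre than local practice did. Nor does the article say that every control-phase woman is delivered at presentation, so some leakage may exist there too. This stands as a limit on size and direction. A reader might infer that the loss must always favour the intervention; the article does not establish that.

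A second reply is that the assumed shares apply to all preterm pre-eclampsia deliveries, whereas only the low-risk branch is advised to defer. Women who are not low risk, and the emergencies kept out of risk stratification, can still be primary events. If, as an assumption, half of the events came from the low-risk branch, a 20% share would require 40% of that branch to leave surveillance and deliver preterm elsewhere. This also stands, and is why the illustration stops at 10%.

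A third is that these women are not lost to the trial. A reader might infer from the primary definition that they have no delivery, neonatal or prolongation outcome. The article does not support that: data are to be collected on every presenting woman and completed by four weeks after the due date, and the secondary outcomes are not confined to in-centre deliveries.

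Finally, sensitivity analyses and database fields usually belong in the full protocol or analysis plan, which are not shown. That is fair for the detail of the remedy. The point itself concerns a primary definition that the article states three times and that the intervention can influence.

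**Conclusion.** The concern holds in limited form. The primary outcome is conditional on delivering in a participating centre, and advice to defer can change that. A preterm pre-eclampsia delivery moved elsewhere would be credited as a reduction. The bias arises only from preterm deliveries elsewhere, and only so far as they are more frequent in the intervention phase than in the control phase.

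The size is unknown. About 1.7 moved deliveries per centre-month would equal the whole target effect, but the documents give no reason to expect that many. The probabilities of 7-8% and 15-20% rest on the assumed 5% and 10% excess shares, no control-phase leakage, no true effect and the assumed ICC and alpha. They show sensitivity and are not forecasts. The stated power is unaffected. This is a moderate point, worth acting on because the remedy is cheap.

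**What to change.** Keep the stated primary outcome. Within the data already to be collected on all presenting women up to four weeks after the due date:

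- Record the place and gestational age of delivery wherever it occurs, in both phases.
- Attribute each woman to her centre and phase of first presentation. This also settles the case of a woman seen at one participating centre who delivers at another; more than one centre lies in Rio de Janeiro.
- Pre-specify one sensitivity analysis of the primary outcome that adds out-of-centre deliveries of presenting women to the denominator and, if preterm with pre-eclampsia, to the numerator.
- Report the share delivered elsewhere by phase.

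If that share is small or similar in both phases, the primary result can be read at face value. The cost is one or two database fields, some effort to trace deliveries at other hospitals, and one more analysis.

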#### Secondary

Secondary outcomes will be:
the proportion of women delivered with preterm pre-eclampsia out of all deliveries for pre-eclampsia;prolongation of pregnancy,proportion of women delivered < 34 weeks’ gestation with pre-eclampsia/total deliveries < 34 weeks’ gestation.

Additional maternal outcomes including
maternal mortality (death in pregnancy or within 42 days of delivery)severe hypertension (systolic BP ≥ 160 mmHg or diastolic BP ≥ 110 mm/Hg),HELLP syndrome,pulmonary edema,eclampsia,stroke,coma,renal or hepatic dysfunction or thrombocytopenia;length of maternal hospital stay

Additional perinatal outcomes will include
fetal death > 20 weeks’ gestation,perinatal death (stillbirth after 27^+ 6^ weeks or early neonatal death < 7 days of birth);Apgar score < 3 at 5 min,respiratory distress syndrome,necrotizing enterocolitis,confirmed sepsis,non-lethal seizures or coma,small for gestational age infants (< 10th and 3rd WHO centile),length of neonatal hospital stay.

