## Background

Pre-eclampsia (PE) is a serious, placentally-mediated disorder that affects about 5% of pregnant women worldwide and represents a major cause of maternal and perinatal mortality [1, 2]. Additionally, the impact of PE on the immediate and long-term health of the infant cannot be overestimated. Apart from perinatal death, preeclampsia is associated with preterm birth (PTB) and fetal growth restriction, with important sequelae of chronic neurological disability and adult cardiometabolic diseases [3–5]. Although several of the pathophysiological features of PE (e.g. reduced placental perfusion, increased inflammation, oxidative and endoplasmic reticulum stress etc.) can contribute to these adverse outcomes, iatrogenic preterm birth persists as a major factor in many countries.

In Brazil, PE causes 23% of all maternal deaths. Once PE has been diagnosed, measures such as antihypertensive therapy and magnesium sulphate may reduce maternal morbidity (such as eclampsia or stroke), but the only ‘cure’ for PE is delivery, regardless of gestational age. For this reason, PE is the indication for almost 18% of all preterm births and nearly half of all iatrogenic premature deliveries [6–9]. In high-income countries (HIC), indicated deliveries for PE are an important contribution to PTB, but account for about 8% [4]. It is possible that many women with mild or equivocal diagnosis of PE may also be delivered inappropriately early in Brazil, often by Caesarean section, owing to imperfect diagnostic and risk stratification methods leading to hasty and unnecessary intervention.

It is evident that the decision for immediate or delayed delivery in women with preterm PE is complex. While immediate delivery serves the interests of the mother, delayed delivery enhances maturation of the fetus and improves neonatal survival rates [10]. [name], one of the co-authors for this work, first developed methods in the United Kingdom more than 30 years ago for the expectant management of PE [11]. Considering the high rates of PTB related to PE in Brazil, a strategic approach for these cases becomes crucial. Therefore, this project aims to test whether the systemic application of an evidence-based risk stratification model can reduce preterm births among women with preterm PE in the country.

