### Inclusion criteria

Women presenting with suspected or confirmed pre-eclampsia between 20 + 0 and 36 + 6 weeks’ gestation at any of the seven tertiary centres will be eligible. Women with any co-morbidity (e.g. chronic hypertension, renal disease, diabetes) will also be included. Pre-eclampsia will be defined as blood pressure (BP) ≥ 140 mmHg systolic or 90 mmHg diastolic on or after 20 weeks of pregnancy, plus proteinuria: more than 1+ on a qualitative dipstick, or ≥ 0.3 g/24 h or urine protein/creatinine > 30 mg/mmol. In the absence of proteinuria pre-eclampsia will be diagnosed if BP ≥ 140/90 mmHg in the presence of any relevant maternal symptoms, signs (e.g., severe hypertension), abnormal maternal laboratory criteria (e.g., low platelets), or abnormal fetal wellbeing (e.g., fetal growth restriction) [29].

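### The < 34-week secondary outcome measures pre-eclampsia's share of early births, not the risk of early delivery with pre-eclampsia, because the intervention can change its denominator

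*Protocol article*

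**What the plan says.** Under Outcome measures, Secondary, the third item is the proportion of women delivered before 34 weeks' "gestation with pre-eclampsia/total deliveries". The sentence then restricts those total deliveries to the ones before 34 weeks. The primary outcome uses a different base, "deliveries with preterm pre-eclampsia/ total deliveries", with no gestational limit on the denominator, and Sample size repeats it. No reason is given for the difference.

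The Intervention section says that the output for low-risk women comes "with recommendations that delivery be delayed unless the clinical condition deteriorates". Eligibility starts at 20+0 weeks and is not limited to confirmed disease: "Women presenting with suspected or confirmed pre-eclampsia between" those limits may enter.

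Data analysis names a mixed effects logistic model with centre, calendar time and exposure for the primary outcome, and says that secondary outcomes are handled in a similar way. It allows either odds ratios or risk ratios. It also lists "gestational age at delivery of all hospital deliveries" among the data to be collected.

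**The concern.** Delivery before 34 weeks is something the intervention is meant to influence. A pre-eclampsia delivery deferred past 34 weeks leaves the numerator and the denominator together. Restricting the denominator to early deliveries therefore conditions on an event that occurs after exposure and may depend on it.

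The ratio answers this question: among births that were early, what fraction had pre-eclampsia? The trial's aim concerns how often women are delivered early with pre-eclampsia. The two can part in size, and even in direction, if early births without pre-eclampsia change as well. At stake is the reading of the one listed secondary outcome that applies the 34-week threshold.

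**Working it through.** **The plan's own figures.** No figure is stated for this outcome. The only power figures, 89.6% (1.5% to 1.0%) and 79.6% (2.0% to 1.5%), belong to the primary outcome. A Hussey-Hughes calculation used 7 centres, 32 months, 4-month steps, 330 deliveries per centre-month and the transition month dropped. With two-sided alpha 0.05 and an ICC of 0.01 to 0.1 (both assumed), it gives 91.3–91.8% and 80.3–81.0% with the variance at the mean of the two rates. With the variance at the baseline rate it gives 85.9–86.5% and 75.0–75.8%. The stated figures lie between these and have no bearing on this point.

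**Inputs**

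- *s*, pre-eclampsia's share of deliveries < 34 weeks before the intervention: not given. Background says "PE is the indication for almost 18% of all preterm births", which covers all births before 37 weeks, and gives about 8% for high-income countries. I use 18% as the reference and 8% to 50% as an assumed range.
- *r*, the factor by which pre-eclampsia deliveries < 34 weeks change: 2/3, borrowed from the primary outcome's design effect, "from a population estimate of 1.5 to 1.0%, representing a 33% risk reduction". The second design effect gives 0.75.
- *g*, the factor by which deliveries < 34 weeks without pre-eclampsia change: 1 if unaffected; 0.9 and 1.1 as illustrations.

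**Formulas**

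- Share afterwards = *rs* / [*rs* + *g*(1 − *s*)]
- Risk ratio of the share = *r* / [*rs* + *g*(1 − *s*)]
- Odds ratio of the share = *r*/*g*

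The odds ratio does not depend on *s*. The risk ratio does, so centres with different shares would show different risk ratios for the same true effect.

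**Step 1: other early births unchanged (*g* = 1, *r* = 2/3)**

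| Share before | Share after | Risk ratio | Apparent reduction | Odds ratio |
|---|---|---|---|---|
| 8% | 5.5% | 0.685 | 31.5% | 0.667 |
| 18% | 12.8% | 0.709 | 29.1% | 0.667 |
| 40% | 30.8% | 0.769 | 23.1% | 0.667 |
| 50% | 40.0% | 0.800 | 20.0% | 0.667 |

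At 18% the sum is 0.12 / (0.12 + 0.82) = 0.128, and 0.128 / 0.18 = 0.709. With *r* = 0.75 at 18%, the share falls to 14.1%: risk ratio 0.785, odds ratio 0.75.

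**Step 2: no effect on pre-eclampsia deliveries, other early births change (*r* = 1, *s* = 18%)**

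- 10% fall: 0.18 / (0.18 + 0.738) = 0.196; risk ratio 1.089, odds ratio 1.111.
- 10% rise: 0.18 / (0.18 + 0.902) = 0.166; risk ratio 0.924, odds ratio 0.909.

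**Step 3: both change (*r* = 2/3, *s* = 18%)**

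- Other early births down 10%: 0.12 / (0.12 + 0.738) = 0.140; risk ratio 0.777, odds ratio 0.741.
- Other early births up 10%: 0.12 / (0.12 + 0.902) = 0.117; risk ratio 0.652, odds ratio 0.606.
- If *g* = *r*, both measures equal 1: a benefit reaching both groups equally would not show at all.

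**Step 4: total deliveries as denominator.** If the total is unchanged, the risk ratio is *r* = 0.667 for any *s*. The odds ratio is about 0.666 at an assumed baseline of 0.5%. Early births without pre-eclampsia affect the result only through the total. If 3% of deliveries are before 34 weeks (an assumption) and 82% of those are without pre-eclampsia, 10% more of them adds 0.03 × 0.82 × 0.10 = 0.25% to the total.

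**The case against.** A reader might infer that this denominator always understates the effect. The article does not support that. The model it names is logistic, and with other early births unchanged the odds ratio equals the true factor exactly. Dilution is a property of the risk ratio, and the article leaves the choice of measure open. If other early births rise with exposure, the effect is overstated.

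The larger dilutions also rest on assumed shares. At the only Brazilian share in the article, 33% reads as 29%, which is modest.

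The model adjusts for centre and calendar time, and the roll-out order is randomised. Fixed differences between centres, and shifts common to all of them, are therefore dealt with. That is correct, but it leaves two routes open. Changes that follow exposure itself are not removed: deferral in women with suspected but never confirmed disease, or knowledge transfer on the hazards of preterm birth. Nor are centre-specific changes that coincide with crossover, which may not average out over seven centres.

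Total deliveries is not an immune base either: a 10% rise in all other deliveries would lower that ratio by about 9% (1/1.1 = 0.909). But such a change concerns a centre's overall volume, which deferral hardly affects.

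Finally, a share of early births is a legitimate measure of burden, and Background uses the same kind of figure for all preterm births. This stands as a reason to keep the share as a description. It does not make it a sound effect measure, and Data analysis sends it through the same kind of model as the primary outcome.

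**Conclusion.** The point holds in a limited form. As defined, the outcome estimates pre-eclampsia's share of early births, on a denominator that contains the numerator and that the intervention can change.

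- With other early births unchanged, a true one-third reduction appears as a risk ratio of about 0.71 at an 18% share and 0.77–0.80 at assumed shares of 40–50%. The odds ratio is not diluted.
- With other early births changing alongside exposure, both measures are distorted, in either direction. For a 10% change at an 18% share, the odds ratio lies between 0.606 and 0.741 and the risk ratio between 0.652 and 0.777, where the truth is 0.667.

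These sizes rest on a < 34-week share that the article does not give and on illustrative 10% changes. Severity is low to moderate: the primary outcome and its sample size are untouched, and prolongation of pregnancy is also listed as a secondary outcome.

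**What to change.** Define the outcome as deliveries before 34 weeks with pre-eclampsia divided by total deliveries, and analyse it with the same model as the primary outcome. Keep the present share as a descriptive measure, reported by exposure beside the count of deliveries before 34 weeks without pre-eclampsia, so that a reader can see which part of the ratio moved.

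The cost is one line in the outcome definition. Gestational age is already to be collected for every hospital delivery, so no new data are needed.
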